#### Secondary Outcomes

The OPQOL-Brief and the CPQ-12 will be analyzed by comparing changes in the scores between the intervention group and the control group. The normality of the data will be assessed using the Shapiro-Wilk test, and equality of the variances between the groups will be assessed via a Q-Q plot and the Brown-Forsythe test. The differences between prestudy and poststudy period assessments in the intervention and control groups will be assessed using pooled variances and a one-sided *t* test. If normality cannot be established or unequal variance is observed within the data, a Q-Q plot will be used to determine the appropriate test (eg, Sign test, Wilcoxon-Signed Rank Test, or Wilcoxon Rank-Sum Test). For all tests, statistical significance will be set at *P*<.05. Quantitative feasibility outcomes (eg, adherence and attrition) will be reported as descriptive data and compared using a one-sided *t* test or a nonparametric equivalent (Mann-Whitney *U* test). All evaluation outcomes will be integrated in a joint display.

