#### Power

This study was designed as a feasibility study for investigating the feasibility of a student-run initiative to reduce loneliness in older adults. A component of this study will be understanding recruitment and retention, which may have significant variability in our sample size. Based on previous studies on interventions to reduce loneliness in older adults, with an effect size of approximately 0.2 and alpha of .05 and 80% power, we expect our sample size to be 196 [43,50-54]. Accounting for attrition rates in other intergenerational programs would be approximately 10%, and the sample size would be 216 [20,55,56]. Since the nature of this study is a feasibility study, which we aim to use to guide a future randomized controlled trial, this feasibility trial is not registered.

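### Secondary outcomes are tested one-sided at an unhalved .05 with no stated direction or reason, and the same one-sided comparison is extended to attendance and attrition, which it does not suit

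*Protocol article*

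**What the plan says.** All of this is in the protocol article, mainly under Statistical Analysis, Secondary Outcomes.

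- **Contrast.** OPQOL-Brief and CPQ-12 "will be analyzed by comparing changes in the scores between the intervention group and the control group".
- **Test.** The pre-post differences in the two arms "will be assessed using pooled variances and a one-sided" *t* test.
- **Level.** "For all tests, statistical significance will be set at" P<.05. The level is not halved for the one-sided tests.
- **Feasibility.** The article says: "Quantitative feasibility outcomes (eg, adherence and attrition) will be reported as descriptive data and compared using a one-sided". The procedure named is again the *t* test, and the Mann-Whitney U test is allowed as the rank-based alternative.

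Elsewhere in the article:

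- The only directional hypothesis, at the end of the Introduction, concerns loneliness and depression.
- Those two primary outcomes are analysed by repeated measures ANOVA or the Friedman test at .05 (Statistical Analysis, Primary Outcomes).
- Outcomes defines adherence as how often family are contacted plus programme attendance, and gives attrition as a rate.
- The abstract and Study Design give the control arm no programme.
- Participant Recruitment expects about 20 participants, 10 per arm.

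**The concern.** The directional tests sit exactly where the article states no directional hypothesis. Where it does state one, for loneliness and depression, the tests are non-directional. A one-sided .05 test has the same favourable-tail threshold as a two-sided .10 test, so the secondary outcomes face a looser standard than the primaries. Evaluation Outcomes plans one joint display with test statistics for all four measures, so a reader would see the two standards side by side. If the tested direction is improvement, worse quality of life among long-term care residents could not be called significant however large it was.

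For feasibility outcomes the difficulty is the kind of data. Attendance exists only where there is a programme to attend. Attrition is yes/no for each participant, sparse at this sample size, and has no stated direction.

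**Working it through.** **Inputs.** About 10 per arm (Participant Recruitment); P<.05 for all tests (Secondary Outcomes); effect size 0.2, 80% power, N = 196, attrition about 10%, N = 216 (Power). I read the secondary *t* test as a comparison between arms, as the contrast sentence and the pooled variance indicate, so df = 10 + 10 − 2 = 18 with everyone analysed.

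**1. The plan's own figure.** Power states: "with an effect size of approximately 0.2 and alpha of .05 and 80% power, we expect our sample size to be 196". The sidedness of alpha is not given.
- Two-sided, one-sample or paired form: ((1.960 + 0.842)/0.2)² = 196.2, which matches.
- One-sided, same form: ((1.645 + 0.842)/0.2)² = 154.6, or 155, which does not.
- Two independent groups: 393 per arm two-sided, 310 per arm one-sided; neither matches.
- Attrition: 196 × 1.10 = 215.6, or 216, as stated.

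So the article's alpha of .05 behaves as two-sided where it can be checked. The formula is inferred, because the article does not print it.

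**2. Sidedness of the secondary tests.**

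| | One-sided .05 | Two-sided .05 |
|---|---|---|
| Critical t, 18 df | 1.734 | 2.101 |
| False-positive risk, favourable tail | 5% | 2.5% |
| False-positive risk, unfavourable tail | 0% | 2.5% |
| At least one favourable false positive in two outcomes, if independent | 1 − 0.95² = 9.75% | 1 − 0.975² = 4.94% |

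Total type I error per test is 5% in both columns. What changes is where it lies.

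**3. Attendance.** Controls have no sessions. Either the control value is missing and no test exists, or it is set to zero. With controls at zero, 10 per arm and eight sessions, a simulation of 5,000 trials rejected in 100% of runs, both at 80% and at 20% attendance in the intervention arm. The test cannot tell good attendance from poor.

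**4. Attrition, example of 0/10 against 3/10.**
- Pooled variance = (10 × 0.3 × 0.7 + 0)/18 = 0.1167.
- SE = √(0.1167 × 2/10) = 0.153.
- t = 0.3/0.153 = 1.96 on 18 df; one-sided P = .033.
- Fisher one-sided = C(10,3)/C(20,3) = 120/1140 = .105; two-sided .21.
- Mann-Whitney in exact form gives the Fisher value, .105. Its normal approximation gives one-sided .034, or .038 with continuity correction.

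**5. Attrition, size of the nominal 5% one-sided *t* test.** Exact binomial enumeration, 10 per arm, non-computable tables counted as no rejection:

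| True attrition, both arms | 5% | 10% | 20% | 30% | 50% |
|---|---|---|---|---|---|
| Size | 0.7% | 2.5% | 4.6% | 5.0% | 5.8% |

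At 10% attrition the chance that nobody drops out is 0.9²⁰ = 12.2%. The variance is then zero and t cannot be computed.

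**The case against.** Much can be said for the plan. Each secondary test still has a total error of 5%, as stated. A direction can be guessed: the abstract presents the programme as raising technology literacy, and the Introduction cites work reporting better quality of life. One-sided testing also buys some power in a very small study: for an assumed standardised effect of 0.5 at 10 per arm, 28% against 18%. The study is a feasibility trial whose Limitations section already expects difficulty in reaching significance, and feasibility outcomes are to be reported descriptively before any test. These points limit the consequences. They do not supply the missing direction or reason, or explain why the primaries, which do have a stated direction, are tested without one.

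Four stronger readings are tempting, and the documents do not support them.

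- **That the *t* test is invalid for attrition.** Its exact size is 2.5% at the article's expected 10% attrition and only 5.8% at 50%. Disagreement with Fisher in one table does not show lost error control, since one-sided Fisher is itself conservative here (size 0.5% at 10% attrition, 2.1% at 50%). The permitted Mann-Whitney route, in exact form, reproduces Fisher; the article does not say which form is meant.
- **That adherence as a whole cannot be compared.** Controls go on interacting with family, so frequency of contact could in principle be compared. Only attendance lacks a control value. The article lists adherence as an example and does not say that each component is tested.
- **That analysing raw change is an error.** Under randomisation it is a valid comparison and already uses the Week 0 score by subtraction.
- **That an attrition P value would mislead the future trial.** Planning would rest on the rates, and those are reported descriptively.

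**Conclusion.** The point holds in a limited form. The firm part is the unjustified one-sided .05 for OPQOL-Brief and CPQ-12: favourable-tail risk of 5% instead of 2.5% per test, and a threshold of 1.734 instead of 2.101. This assumes a between-arm *t* test with 10 analysed per arm; the doubling of the tail does not depend on the sample size. The inability to declare a fall in quality of life assumes that the unstated direction is improvement.

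A between-arm test of attendance carries no information. One sentence under enTECH Intervention and Study Procedure has both groups completing a final intervention session; it conflicts with the abstract and Study Design and needs to be reconciled with them, but does not give controls a programme.

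For attrition, the *t* test is poorly suited and sometimes not computable, without gross inflation of its size. All of this touches secondary and feasibility outcomes only, so it should be changed but does not threaten the primary analysis.

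**What to change.** In Secondary Outcomes:

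1. Test OPQOL-Brief and CPQ-12 two-sided at .05 and report the difference between arms with a 95% CI. Preferably use ANCOVA of the Week 8 score on arm and the Week 0 score. Both scores are already collected, so any gain in precision is free; it improves efficiency and does not repair an error.
2. Describe programme attendance in the intervention arm only.
3. Report attrition in each arm as a proportion with an exact 95% CI. If the arms are compared, use a two-sided Fisher exact test.

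The cost is wording only, with no new data and no change to conduct. Secondary P values become slightly less favourable. The trial was halted with 8 participants recruited, so the text can be settled before it restarts.

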### Randomization and Blinding

After the consenting process, participants will be randomized to either the intervention or the control group by using a computer-generated allocation sequence in a 1:1 ratio. If randomized to the intervention group, researchers will work with the participants to obtain a family member’s email address for use in the study. Owing to the nature of the study, participants cannot be blinded to allocation. Two separate research teams will facilitate the study. The clinical team will be carrying out the intervention, while the research team will be conducting the interviews and administering the scales. In order to maintain participant confidentiality and anonymity to the interviewers, participants will be assigned a participant ID number via the allocation sequence described above. This number will be known to both the clinical team and the research team; however, the research team will not be able to see the participants in the intervention group or those in the control group. When data are entered into the computer, the data will be associated with the participant IDs alone.

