#### Participant Recruitment

Participants will be recruited through a long-term care home in Southern Ontario. Recreational facilitators will assist in recruiting participants for the study. Moreover, brochures, pamphlets, and flyers (Multimedia Appendix 2) will be placed in the study location by the team, in addition to a town hall advertising the study. Potential participants will be asked 2 questions to determine eligibility: if they currently use email/texting/messaging to contact family members and if they believe a family member would be willing to respond to an email sent by them once a week (Multimedia Appendix 3). Collecting the contact information of the participants’ family members requires balancing of respect for the participants’ autonomy, along with their potential comfort with the study’s subject matter. After consenting, participants will be presented with 2 options so that the research team can contact their family members. One option will consist of the participant providing the research team with a ranked list of family members to potentially receive emails from the participant, along with their phone numbers. The other option will consist of providing the participants with an information sheet, written in layperson terms, which they can use to describe the study to the family members to ask if they would like to participate. Members of the research team will follow up after 3 days to see if the participants were able to contact their family members or to provide support to facilitate this contact. The research team will then offer to contact the family member on their behalf, and at such time will record the contact information of up to 3 family members and contact them using the telephone script (Multimedia Appendix 4). Recruitment for the study started in November 2019. We expected to enroll approximately 20 participants, 10 in each condition. We successfully enrolled 8 participants before the study was forced to halt due to the COVID-19 pandemic (Multimedia Appendix 5).

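### For the secondary outcomes a Q-Q plot is used to check for unequal variances and to choose the remedy, which it cannot do, and no named fallback test copes with them

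*Protocol article*

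**What the plan says.** The rule is in the protocol article, Statistical Analysis, Secondary Outcomes. OPQOL-Brief and CPQ-12 "will be analyzed by comparing changes in the scores between the intervention group and the control group". Normality is checked with the Shapiro-Wilk test, and "equality of the variances between the groups will be assessed via a Q-Q plot and the Brown-Forsythe test". By default the pre-to-post differences "will be assessed using pooled variances and a one-sided *t* test". The fallback reads: "If normality cannot be established or unequal variance is observed within the data, a Q-Q plot will be used to determine the appropriate test", with these candidates: "eg, Sign test, Wilcoxon-Signed Rank Test, or Wilcoxon Rank-Sum Test". The level is fixed too: "For all tests, statistical significance will be set at *P*<.05".

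Two other sections bear on arm sizes. Participants are randomised "by using a computer-generated allocation sequence in a 1:1 ratio" (Randomization and Blinding), and on numbers: "We expected to enroll approximately 20 participants, 10 in each condition" (Participant Recruitment). The Power section takes attrition to be about 10%. The document gives no standard deviation for change on either scale and does not say whether the allocation sequence is blocked.

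**The concern.** The aim is to compare change between two independent arms, and the fallback has two triggers: non-normality or unequal variance. Under the second trigger the rule fails in three ways.

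- A Q-Q plot compares the quantiles of a sample with those of a reference distribution. It is a check on shape. It does not assess equality of variance between arms, and it cannot select a test that corrects for inequality. The protocol gives it both jobs.
- The sign and signed-rank tests are one-sample or paired tests. Applied within an arm, they leave the other arm out and so miss the stated aim.
- The rank-sum test does compare the arms but, read as a test of location, it requires the same spread in both.

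The usual answer to unequal variances, Welch's t test, is not named. At stake is whether the stated 5% level holds when arms differ in both size and spread. Some difference in spread is plausible for CPQ-12, since only one arm is taught and no computer-proficiency exclusion applies, but that is conjecture, and there is no comparable argument for OPQOL-Brief.

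**Working it through.** **Inputs from the protocol.** One-sided test, 5% level, pooled variance, 1:1 allocation, about 10 per arm, about 10% attrition.

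**Assumed inputs.** Normal change scores with no true difference, and SD ratios of 2 and 3 between arms. The document gives no SDs.

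**1. Why unequal arms matter for the pooled test.** The true variance of the difference in means is V = s1²/n1 + s2²/n2. The pooled test targets P = sp²(1/n1 + 1/n2), where sp² = [(n1−1)s1² + (n2−1)s2²]/(n1+n2−2). Arm 1 is the more variable arm, and arm 2 has SD 1.

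| Arms (1 v 2) | SD of arm 1 | V | P | √(P/V) |
|---|---|---|---|---|
| 10 v 10 | 2 | 4/10 + 1/10 = 0.500 | 2.500 × 0.2 = 0.500 | 1.00 |
| 8 v 12 | 2 | 4/8 + 1/12 = 0.583 | (39/18) × 0.2083 = 0.451 | 0.88 |
| 8 v 12 | 3 | 9/8 + 1/12 = 1.208 | (74/18) × 0.2083 = 0.856 | 0.84 |
| 12 v 8 | 2 | 4/12 + 1/8 = 0.458 | (51/18) × 0.2083 = 0.590 | 1.13 |
| 12 v 8 | 3 | 9/12 + 1/8 = 0.875 | (106/18) × 0.2083 = 1.227 | 1.18 |

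The pooled standard error is right at equal sizes, 12%-16% too small when the smaller arm is the more variable, and 13%-18% too large in the reverse case.

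**2. The whole rule, simulated.** If Shapiro-Wilk in either arm or Brown-Forsythe rejects, the exact rank-sum test is used; otherwise the pooled t test, one-sided at 5%. Runs were 8,000 per setting in two of the sets below, so the Monte Carlo standard error is about √(0.07 × 0.93/8000) = 0.3 points.

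- Baseline: 10 v 10 with equal SDs gives 5.3%, so the rule reproduces the nominal level when its assumptions hold.
- 10 v 10, SD ratios 2-3: 4.6%-5.6% across separate sets of runs.
- 8 v 12, smaller arm more variable: 7.1% and 7.7% at ratios 2 and 3 in one set, 7.6% and 7.1% in another.
- 12 v 8, larger arm more variable: 4.0% and 3.4%, and 4.0% and 3.2%.
- Welch's test in the runs at these sizes: 4.5%-5.6%.

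**3. The variance pre-test.** Brown-Forsythe detects an SD ratio of 2 in 30% of runs and a ratio of 3 in 65% at 10 v 10. At splits of 8 v 11 and 7 v 12, in either direction, it detects 21%-29% and 49%-62%. At ratio 2, therefore, it usually misses the inequality.

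**4. The rank-sum test alone (one-sided, ratios 2 and 3).** 10 v 10: 4.9%, 5.5%. 8 v 10: 5.4%, 6.2%. 7 v 12: 6.2%, 7.0%. 12 v 7: 3.2%, 3.6%. It misses 5% in the same directions as the pooled test.

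**5. A within-arm test.** If both arms drift by an assumed 0.5 SD with no treatment effect, a one-sided signed-rank test in one arm of 10 rejects about 37% of the time.

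**6. How often the arms would be uneven.** If the sequence were unrestricted, Binomial(20, 0.5) gives exactly 10/10 with probability 0.176 and 8/12 or worse with probability 0.503. If arms start at 10/10 and each participant drops out with probability 10%, sizes differ by 4 or more in only about 1% of trials. Averaged over simple randomisation, the rule's error was 4.6% and 5.8% at ratios 2 and 3; averaged over 10/10 with 10% dropout it was 5.7% at both (5,000 runs each). Another set of runs put these averages at 5.4%-5.9%.

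**The case against.** The strongest reply is that the stated design is 10 v 10, where the rule is close to nominal. An 8 v 12 split with a two- or threefold SD ratio is a selected case, and over the sizes likely to arise the over- and under-rejection largely cancel. That stands. A reader might infer that the 5% level fails under this plan in general, or that half of such trials would split 8/12 or worse. The document supports neither: the first holds only given an unfavourable split, and the second needs an unrestricted sequence, which the article neither states nor excludes.

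A second reply is that the list of tests is introduced as examples, so Welch's test is not barred. This is true, but every example is a sign or rank test and the selector is a Q-Q plot, so a reader following the text would not be led to Welch.

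A third concerns the remedy. It is tempting to say that Welch should be used in every case and would always hold 5%. It would not. With exponential changes and unequal SDs, its one-sided error reached about 14% in one direction, and its two-sided error ran at about 5%-10% (rank-sum: 8%-17% two-sided). With very small arms it drifts too, to about 5.8% one-sided at 3 v 5. Welch answers the unequal-variance trigger; the non-normality trigger in the same sentence needs its own rule.

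**Conclusion.** The concern holds as a flaw in a stated rule, with a modest and conditional numerical effect. That a Q-Q plot cannot check or remedy unequal variances, and that none of the named tests remedies them in a between-arm comparison, follows from what these methods do and needs no assumption about the data. The size does rest on assumptions: normal changes, SD ratios of 2-3 and the arm sizes shown. Under these, the one-sided error is near 5% at the planned sizes, about 5%-6% averaged over simple randomisation or 10% dropout, about 7%-8% at 8 v 12 with the smaller arm more variable, and about 3%-4% in the reverse case. The document gives neither the SDs nor the type of sequence, so these figures are illustrations and not predictions for this trial. Severity is minor: the outcomes are secondary and the study is a feasibility trial.

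**What to change.** In Secondary Outcomes:

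- Replace the pooled-variance t test by Welch's unequal-variance t test on the change scores as the default, with no variance pre-test.
- Remove the Q-Q plot as a check of variances and as a selector of tests.
- For marked non-normality, prespecify one between-arm method, for example the rank-sum test, reported as a comparison of distributions and not of means or medians.
- Drop the sign and signed-rank tests for the between-arm comparison.

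The cost is wording only and can be met before recruitment resumes. If the variances are in fact equal, the loss of power is negligible: with equal arm sizes the Welch and pooled t statistics are identical and only the degrees of freedom differ.

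### The nonparametric fallback for OPQOL-Brief and CPQ-12 lists two paired tests that cannot compare the arms, and a Q-Q plot cannot steer the analyst to the one test that can

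*Protocol article*

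**What the plan says.** All of the analysis text is in the protocol article, Statistical Analysis, Secondary Outcomes.

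- **The question.** The two scales "will be analyzed by comparing changes in the scores between the intervention group and the control group".
- **The main test.** Pre-post differences "in the intervention and control groups will be assessed using pooled variances and a one-sided" t test. Pooling variances makes this a two-sample test.
- **The trigger for the fallback.** "If normality cannot be established or unequal variance is observed within the data".
- **The fallback.** "a Q-Q plot will be used to determine the appropriate test (eg, Sign test, Wilcoxon-Signed Rank Test, or Wilcoxon Rank-Sum Test").
- **The threshold.** "For all tests, statistical significance will be set at *P*<.05".

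Under Randomization and Blinding, participants are allocated "by using a computer-generated allocation sequence in a 1:1 ratio", and no matching is described, so the arms are independent. Under Participant Recruitment the planned size is given: "We expected to enroll approximately 20 participants, 10 in each condition".

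**The concern.** The three tests are listed as alternatives, but they do not test the same hypothesis. With independent arms, the Sign and signed-rank tests can be applied only to pre-post differences, within one arm or pooled over both. Their null is zero change. The null that the section sets up is equal change in the two arms, and of the three only the rank-sum test on change scores addresses it.

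The stated selector does not protect against a wrong choice. A Q-Q plot can suggest whether changes are symmetric or skewed, which helps to choose between signed-rank and Sign, the two tests that leave the control arm out. It carries no information on whether arms are being compared.

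A shared change is plausible here. Both questionnaires are given to both arms before and after the study period, controls have access to public computers and recreational therapists (Study Design), and there is only one site (Limitations). The reverse error is also possible: if the programme keeps scores steady while controls decline, a test within the intervention arm sees nothing. The section Evaluation Outcomes puts test statistics for all four measured variables into the joint display, so the wrong statistic would be on show.

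**Working it through.** The plan gives no figure to reproduce on this point. The check is what the stated rule does when followed from trigger to test.

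**Inputs from the article:** 10 per arm, independent arms, one-sided test at .05, pooled-variance t test unless normality or equal variance fails.

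**Assumptions, not in the article:** Shapiro-Wilk in each arm and Brown-Forsythe, each at .05, as the trigger; a shared shift of 0.3, 0.5 or 0.8 SD of the change score; changes either normal or centred exponential (skewed). For the first two steps the true between-arm difference is zero.

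**Step 1: the tests alone, ignoring the trigger.** Rejection rates at shifts of 0.3/0.5/0.8 SD:

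| Test | Normal | Skewed |
|---|---|---|
| Signed-rank, intervention arm | 19% / 39% / 71% | 8% / 31% / 90% |
| Sign, intervention arm | 6% / 14% / 34% | 0.4% / 6% / 42% |
| Rank-sum between arms | about 5% | 4-5% |

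These rates apply only once the fallback has been reached and a paired test chosen.

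**Step 2: the whole rule.** The fallback is reached in about 13% of trials with normal changes and about 72% with skewed changes. Overall false-positive rates:

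| Fallback used | Normal | Skewed |
|---|---|---|
| Signed-rank | 7% / 10% / 12% | 7% / 21% / 65% |
| Sign | 5% / 6% / 10% | 2% / 5% / 32% |
| Rank-sum | about 5% | about 5% |

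Separate simulation runs differ slightly (9-10% and 12-14% for the two larger normal shifts).

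A rough hand check treats trigger and test result as independent: overall rate ≈ P(fallback) × paired-test rate + [1 − P(fallback)] × 5%.

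- Normal, 0.5 SD: 0.13 × 0.39 + 0.87 × 0.05 = 0.051 + 0.044 = 0.09.
- Normal, 0.8 SD: 0.13 × 0.71 + 0.87 × 0.05 = 0.092 + 0.044 = 0.14.
- Skewed, 0.5 SD: 0.72 × 0.31 + 0.28 × 0.05 = 0.223 + 0.014 = 0.24.
- Skewed, 0.8 SD: 0.72 × 0.90 + 0.28 × 0.05 = 0.648 + 0.014 = 0.66.

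These agree with the simulated values to within about 3 percentage points.

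**Step 3: the reverse error.** The intervention arm is stable and controls decline by 1.0 SD. Overall power with signed-rank as fallback is about 60%, against 68% with rank-sum, for normal changes; it is 24% against 82% for skewed changes. The skewed loss is what one expects when 72% of trials go to a test with almost no power for this difference: 0.28 × 0.82 = 0.23.

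**Step 4: the sample so far.** If the 8 enrolled participants are split 4 and 4, the smallest one-sided p-value of either paired test is (1/2)^4 = 1/16 = 0.0625. Neither can then reach .05, so the false-positive risk belongs to the planned 10 per arm.

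**The case against.** The strongest defence is that the plan does not commit to the error. Its opening sentence fixes a between-arm question, the list is introduced as examples, and the rank-sum test is among them. The paired tests may have been meant for within-arm change, which the Primary Outcomes section names openly as an aim. The Secondary Outcomes section itself gives Mann-Whitney as the nonparametric equivalent of the t test for feasibility outcomes. These points stand as far as they go. A reader might infer that the control group drops out of the analysis; the text does not support that, because it happens only if one of the two paired options is picked.

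A reader might also take the 39% or 71% in Step 1, or the 4% power that signed-rank has alone when normal controls decline by 1.0 SD, as the plan's error rates. They are not. With normal, equal-variance changes the two-sample t test is used in most trials, and the overall figures are those in Steps 2 and 3. Regression to the mean is also a weak explanation for a shared change, since nobody is selected on OPQOL-Brief and computer proficiency is not an exclusion criterion.

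The defence does not remove the defect. No sentence limits the paired tests to description: they replace the main test, and the same significance threshold covers all tests. Nor is this a detail left to an analysis plan, because the article names the tests and two of them do not fit its own question. Running signed-rank in each arm and contrasting the verdicts is no rescue: with normal changes and a shared shift of 0.5 SD, it is significant in the intervention arm and not in the control arm in 23.6% of simulated trials in which it is applied.

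**Conclusion.** The point holds in a limited form. The stated fallback permits two tests that cannot answer the stated question, and its selector cannot screen them out. For normal changes the harm is modest, because the fallback is seldom reached: about 7% to 12% false positives where 5% is intended. It becomes material where the fallback is meant to operate. With skewed changes and signed-rank chosen, false positives are about 7%, 21% and 65% at shared shifts of 0.3, 0.5 and 0.8 SD, and power falls from 82% to 24% when controls decline by 1.0 SD.

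These figures rest on the assumed trigger, on assumed shifts for which the article gives no value, on an exponential shape standing in for skewness, and on the paired test being chosen every time the fallback is reached. Weight: minor to moderate. These are secondary outcomes of a feasibility trial, and the Limitations section already expects statistical significance to be hard to reach.

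**What to change.** In Secondary Outcomes, remove the Sign test, the signed-rank test and selection by Q-Q plot from the between-arm fallback. Replace them with wording such as: if normality fails, pre-to-post change scores will be compared between arms with the Wilcoxon rank-sum (Mann-Whitney) test; if only the variances differ, Welch's t test on the change scores will be used; any within-arm test is descriptive. A Hodges-Lehmann difference with its interval is optional.

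One limit should be acknowledged: when changes are both non-normal and unequal in variance, the rank-sum test need not hold its nominal level exactly, though it still compares the arms.

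The cost is one sentence, with no extra data, participants or staff, and the study is halted, so the change can be made before restart. What is given up is the option of presenting a within-arm improvement as the significance test.
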